## Abstract

**Background:**

Chronic diseases are a significant and growing problem of our time. They impair the ability to work and increase the risk of early retirement. To support the return to work, rehabilitation services can be applied for in Germany. Currently, the application system for rehabilitation allows only a limited degree of individualisation of the treatment and is associated with a lack of multidisciplinary communication. To facilitate rehabilitation care planning, we developed a complex intervention. A digital, platform-based case management approach (intervention) will ensure multidisciplinary communication and the tailored selection of medical treatments and/or non-medical support measures. The overall objective is to assess the effectiveness of the intervention compared to treatment as usual (control condition). The German Federal Ministry of Labour and Social Affairs (BMAS) funds the RehaPro-SERVE study (grant number: 661R0053K1).

**Methods:**

This is the protocol for an investigator-initiated, pragmatic, multicentre, randomised and controlled two-arm parallel-group superiority trial with embedded qualitative process evaluation. The study will be conducted in Hesse state, Germany. *N* = 59 primary care physicians will be recruited and tasked with the recruitment of six eligible patients each. Eligibility criteria: age 40–60; minimum of 4-week work disability due to musculoskeletal, oncologic or psychological conditions or the post-COVID-19 syndrome within the last 6 months; at high risk for early retirement. In total, *n* = 352 patients will be randomised with a 1:1 allocation to intervention or control group and stratified by primary care practice using permuted blocks. The primary outcome is the number of days of sick leave during a 12-month period after the assumed completion of treatments (t1 to t2). Secondary outcomes include the number of days of sick leave (self-report), work ability, and health-related quality of life, as well as data from the qualitative process evaluation.

**Discussion:**

The results of the study will inform the design of future care services and provide valuable information on multidisciplinary case management in the context of rehabilitation care planning. The results of the qualitative process evaluation will further contribute to the understanding of facilitating and hindering factors.

**Trial registration:**

DRKS-German Clinical Trials Register, DRKS0 00242 07. Registered on 22 March 2021.

**Supplementary Information:**

The online version contains supplementary material available at 10.1186/s13063-024-08571-2.

## Administrative information

The numbers in curly brackets in this protocol refer to SPIRIT checklist item numbers. The order of the items has been modified to group similar items (see http://www.equator-network.org/reporting-guidelines/spirit-2013-statement-defining-standard-protocol-items-for-clinical-trials/)

## Introduction

### Background and rationale {6a}

Reports show that chronic diseases are on the rise in high-income countries [1]. While they have a substantial impact on the quality of life of those affected [2, 3] and are associated with reduced work ability [1], they also represent a risk factor for early retirement [1]. In Germany, rehabilitation offers an opportunity for tertiary prevention and has shown to be effective in supporting patients with oncological, musculoskeletal or mental disorders in their return to work [4–6]. Working-age people can apply for rehabilitation therapies from the German pension insurance, which is usually responsible for approving and providing medical rehabilitation if patients have accumulated at least 5 years of pension contributions and their work ability is reduced or at risk. The application process is initiated by the patients themselves, the attending primary care physician (PCP) or other specialised physician [7, 8]. The PCP usually assists in the preparation and submission of the application and also sends a medical report to the German pension insurance [7, 8]. If personal (e.g. reduced working ability) and insurance law requirements (e.g. insurance period) are met, the application can be approved. Approved rehabilitation can take place on an outpatient or inpatient basis, with inpatient rehabilitation accounting for around 80% in Germany [9]. Inpatient stays usually span 3 weeks and consist of a combination of different treatment elements like medical treatments, exercise therapy, health education, psychological counselling, relaxation techniques, occupational therapy, work-related interventions or socio-legal counselling. Due to the legal requirements and approval of therapies from pension insurance services only, the current system only supports individualisation of the therapy to a very limited extent. However, patients consider a good fit between the design of the rehabilitation therapy and their individual needs an important factor in the evaluation of rehabilitation [10]. Further problems, counteracting an easy access to rehabilitation therapies, are seen in the application and approval process by PCPs. In particular, the process is perceived as time-consuming [7, 11], bureaucratic [7, 11] and non-transparent [11, 12]. Communication deficits and a lack of interdisciplinary coordination are also reported [7, 11, 12]. However, approaches that use multidisciplinary care planning improve functional outcomes for people with chronic or complex care needs [13] and strategies to improve communication across disciplines are associated with improved health and patient satisfaction [14]. Digital solutions, such as platform-based approaches, could provide useful support for care planning and facilitate communication between different stakeholders [15–18].

This paper describes the design of the RehaPro-SERVE study, an investigator-initiated, pragmatic, multicentre, randomised and controlled two-arm parallel-group superiority trial with an embedded process evaluation including an interview study. Through a platform-based case management approach, the study aims to facilitate rehabilitation care planning. A complex intervention [19] was developed that involves multidisciplinary communication and enables the tailored selection of appropriate rehabilitation therapy, medical treatments (MT) or non-medical support measures (NMSM). The digital platform-based solution also ensures communication between stakeholders in an efficient and timely way. The study will compare this new approach to rehabilitation care planning with routine care.

### Objectives {7}

The overall objective is to assess the effectiveness of the developed platform-based case management approach (intervention condition) for rehabilitation care planning compared to treatment/care planning as usual (control condition).

The primary estimand is defined by the following attributes:Treatment condition: assignment to platform-based case management approach (intervention condition) for rehabilitation care planning compared to treatment/care planning as usual (control condition) including the effects of withdrawal from rehabilitation care.Target population: adults aged 40 to 60 years with a minimum of 4-week (20 workdays) work disability due to musculoskeletal, oncologic or psychological conditions or the post-COVID-19 syndrome (PCS) within the last 6 months prior to study inclusion (patient-reported information) and a high risk of early retirementEndpoint: cumulative sick leave days, health insurance data, during the period of 12 months after completion of the treatment (t1 to t2).Intercurrent events and strategies to address them: plausible and important intercurrent events include the patients’ withdrawal from the rehabilitation due to any reason, are addressed in the treatment condition attribute and handled with the treatment policy strategy.

The secondary estimands differ from the primary only in regard to the endpoints: self-reported cumulative sick leave days during the period of 12 months after completion of the treatment (t1 to t2); work ability, as measured by the Work Ability Index (WAI, German version) [20] and the health-related quality of life, as measured by the Short Form 36 Health Survey (SF-36, German version) [21, 22] 12 months after completion of the treatment (t2).

We also aim to describe the delivered process in terms of adherence, use of treatments (MT/NMSM), implementation of the intervention, treatments (MT/NMSM) recommended on the digital platform as well as involvement of a social worker. Moreover, facilitating and hindering factors that influence the success of the intervention and to identify adaptations that are necessary for a successful implementation will be investigated qualitatively as a part of the process evaluation.

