### Outcomes {12}

The primary outcome is the total numbers of days of sick leave between t1 and t2 (12-month period after the assumed completion of treatment (MT/NMSM)). The time points for assessments are presented in Table 1.

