#### Primary outcome

Number of days of sick leave: postal enquiry health insurance (time periods inquired: 6 months before baseline till t0, t0 till t1, t1 till t2). Patients will receive a prepared form and a stamped envelope so that the request can be sent to their health insurance directly after signature. The aggregation method for both groups will be the mean number of sick days between t1 and t2 assessed at t2.

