### Participant timeline {13}

Eligible PCPs will be asked to sign informed consent (Additional file 2) and then complete a short questionnaire containing demographic and practice characteristics. Afterwards, they will start screening for eligible patients. Data will be collected at three time points: baseline (t0), 6 months (t1) and 18 months (t2) during personal or telephone appointments with a research assistant. We expect CCs or other application procedures, waiting times and possible treatments (MT/NMSM) to be completed 6 months after baseline (t1). The time schedule of patients' enrolment, interventions, and assessments is displayed in Table 1.

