A limitation is the randomisation technique stratified by primary care practice and using permuted blocks of six (as this is the number of patients to be recruited in the practices). By this design, allocation concealment will not be given for the last (sixth) patient recruited in a practice. This increases the risk of selection bias [43]. Another limitation of the chosen randomisation method is that not all PCPs may be able to recruit six patients. In this case, the equal distribution of patients to both groups would no longer be given. It can also be argued that spill-over effects may occur, as the focus of participating PCPs may have a greater emphasis on the rehabilitation care and intervention planning than without the study. This may also accelerate or initiate processes in the control group. Also, if the study finds differences between the groups, this would be even more indicative of an intervention effect. However, a spill-over effect could also hide the true effect (Type II error). In order to reduce spill-over effects, the use of cluster randomisation was also discussed. Ensuring the chronology of such randomisation (first recruitment, then randomisation) did not appear feasible in the context of the study (long recruitment periods lead to longer waiting times for patients). Without adherence to this chronology, there would be no allocation concealment at all and the risk of recruitment bias would be increased [44]. Therefore, we decided on the stratified randomisation. Also, an equal distribution of workload for PCPs is given.

Another limitation is, that there will be no control of whether the in the CC recommended treatments (MT/NMSM) are actually used. It should be noted that the intervention is particularly about the application and decision-making processes and the offer of treatments (MT/NMSM). Similarly, only these can be influenced within the framework of the study. However, when a person can actually participate in a rehabilitation or other intervention depends on a number of further factors, such as the availability of rehabilitation care slots.

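### The estimand dates the endpoint from completion of treatment, but the measured window is a fixed months 6 to 18, so a difference may partly be absence moved across month 6 rather than avoided

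*Protocol article*

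**What the plan says.** All references are to the protocol article.

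- **Objectives {7}** gives the primary endpoint as "cumulative sick leave days, health insurance data, during the period of 12 months after completion of the treatment" and labels the period t1 to t2. The secondary estimands are dated from completion in the same way.
- **Participant timeline {13}** sets the assessments at "baseline (t0), 6 months (t1) and 18 months (t2"). The link between t1 and completion is an expectation: "We expect CCs or other application procedures, waiting times and possible treatments (MT/NMSM) to be completed 6 months after baseline (t1").
- **Outcomes {12}** is more careful and speaks of a "12-month period after the assumed completion of treatment (MT/NMSM"). The Abstract and Sample size {14} also call the completion or end of treatment assumed.
- **Discussion** says that when a person can take part in a measure "depends on a number of further factors, such as the availability of rehabilitation care slots".
- **Primary outcome** lists what is requested from the insurer: "time periods inquired: 6 months before baseline till t0, t0 till t1, t1 till t2". The primary outcome, the self-report outcome and the model in Statistical methods {20a} use the sum from t1 to t2. The days from t0 to t1 enter no stated outcome.
- **Process evaluation** (under Outcomes {12}) collects start and end dates of measures at t1 and t2, and the time from baseline to the first measure.

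**The concern.** Two things do not fit together.

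First, the estimand as worded starts the clock when a patient completes treatment, while the data start it at month 6 regardless. For a patient who takes up no measure, which item {20c} accepts for both groups, the literal endpoint has no starting date.

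Second, the fixed line at month 6 may interact with what the intervention does. Background and rationale {6a} calls the usual application route time-consuming. The trial's aims and Intervention description {11a} present the platform as quicker in communication and wider in access. Controls may still apply on paper forms. If the arms differ in when, or how often, patients are absent for a measure, that absence can fall before month 6 in one arm and after it in the other. Only the part after month 6 is counted, so no stated outcome separates absence avoided from absence moved. At stake is the reading of the primary result as a gain in working time.

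**Working it through.** **The plan's own figures.** Sample size {14} assumes a 34-day difference, SD 90 days, a two-sided 5% t-test and 90% power. The standardised difference is 34/90 = 0.378. The t-test needs 148.2, so 149 per arm, with power 90.2% at 149. For 15% dropout, 149/0.85 = 175.3, so 176 per arm and 352 in total. Both stated figures reproduce, and nothing below changes them.

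**Inputs for the shift**

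- Length of a stay, L: three weeks is usual for inpatients (Background and rationale {6a}). That is 21 calendar days. It is 15 workdays on the convention of the eligibility criteria, which equate four weeks with 20 workdays.
- Excess share, f: the proportion of control *patients* with a stay after t1, minus the same proportion in the intervention arm. The documents give no timing by arm, so f is an assumption shown over a range.
- Further assumptions: stay days are recorded as sick leave (the documents do not say), each stay lies wholly on one side of month 6, and total sick leave from t0 to t2 is equal in the two arms.

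**Formula.** Shift in the t1 to t2 contrast = L × f. The last column is the probability that the planned t-test with SD 90 and 149 per arm gives p < 0.05 from the shift alone.

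| f | Shift, L = 15 to 21 | Share of 34 days | P(p < 0.05) |
|---|---|---|---|
| 10% | 1.5 to 2.1 days | 4% to 6% | 5.2% to 5.5% |
| 25% | 3.75 to 5.25 days | 11% to 15% | 6.5% to 7.9% |
| 50% | 7.5 to 10.5 days | 22% to 31% | 11.1% to 17.1% |
| 100% | 15 to 21 days | 44% to 62% | 30.0% to 51.9% |

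The 100% row is a ceiling, not a scenario. A moved stay alone cannot produce 34 days. A negative f reverses the sign and counts against the intervention. The probabilities refer to the planned size; Trial status reports that recruitment ended early and gives no number reached.

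**Patients or stays.** If f is instead the difference in the share of *stays* falling after t1, it must be multiplied by the uptake u in each arm: shift = L × u × f. With u = 50% in both arms and f = 10%, this gives 15 × 0.5 × 0.10 = 0.75 days to 21 × 0.5 × 0.10 = 1.05 days, half of the first row.

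**What is left out.** Extra sick leave because a patient waits longer for a measure is not moved absence. It is a real difference in total days, and a t0 to t2 sum would count it as such.

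**The case against.** The strongest reply is that nobody could mistake the window. Objectives {7} adds the label t1 to t2, the timeline fixes both points, and three other places call the completion assumed. That stands: the operational definition is clear, and the wording alone would be an editorial matter. A reader might infer that the trial measures something incompatible with its estimand, but the documents do not support that.

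The next reply is that a window anchored to baseline and identical in both arms gives a valid randomised comparison, and that allowing six months for treatment is a disclosed design choice. That also stands. What remains is a limit on interpretation.

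A reader might further infer that the window flatters the intervention. The documents do not establish the direction. Slot availability is not specific to an arm. Controls need not apply, so many may have no stay to move. Intervention patients may receive vocational or other measures that routine care would not give them; if these start after t1 and involve absence, they count against the intervention.

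Finally, a supportive analysis might be left to an analysis plan that is not shown, and the treatment dates are already to be described in the process evaluation. This limits the weight of the point. It does not remove the reason to report the t0 to t2 sum beside the primary result, because the article's stated outcomes all exclude t0 to t1.

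**Conclusion.** The point holds in a limited form. The estimand names completion of treatment, whereas the trial measures months 6 to 18 after baseline. The comparison of that window is valid, but the stated outcomes cannot show how much of a difference is absence avoided and how much is absence moved across month 6. The shift may go either way.

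Its size is unknown. The figure of 1.5 to 2.1 days per 10 percentage points of excess control patients illustrates scale and is not a forecast. It rests on stay days counting as sick leave and on a three-week stay, and it is proportionally smaller if the excess is a share of stays and uptake is below 100%.

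The rewording is editorial. The supportive analysis is what adds to the conclusions the trial can draw.

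**What to change.** 1. In Objectives {7}, word the primary endpoint as insurer-recorded sick-leave days from month 6 to month 18 after baseline, with month 6 described as the assumed completion of treatment. Align the secondary estimands, which use the same phrase.
2. Leave the primary analysis and the sample size as they are.
3. Pre-specify cumulative insurer days from t0 to t2, fitted with the same model, as a supportive analysis reported beside the primary result. Who will be blinded {17a} has the analysis plan finalised while the statistician is still blinded, so it can be fixed there.
4. Tabulate by arm the share of patients with a measure running at t1 or starting after it, from the start and end dates already collected.

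The cost is a wording change, one table and one more model run, with no new data collection. The t0 to t2 sum is noisier because it includes the treatment period, which is a reason to keep it supportive.

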### Trial design {8}

The RehaPro SERVE Trial is an investigator-initiated, pragmatic, multicentre, randomised and controlled two-arm parallel-group superiority trial. Initially, PCPs will be recruited by the study team, enrolled in the study and tasked with recruiting patients with musculoskeletal, oncological or psychological conditions or PCS. Patients will be randomised using a 1:1 allocation to either the intervention group (rehabilitation care planning with a multidisciplinary platform-based case management approach) or the control group (treatment as usual) stratified by primary care practice and using permuted blocks. A parallel process evaluation will be completed, which will examine adherence, treatment decisions (MT/NMSM), implementation of the intervention, as well as involvement of the social worker. An interview study will be part of the process evaluation and will be conducted with PCPs, patients and other stakeholders involved in the intervention (public health physician, case administrator and social worker), to qualitatively investigate facilitating and hindering factors which influence the success of the intervention and to identify adaptations that are necessary for successful implementation. Reporting of the study will follow the CONSORT guidelines for reporting parallel group randomised trials [23].

## Methods: participants, interventions and outcomes

### Study setting {9}

Recruitment will take place in the setting of primary care in the state of Hesse (Germany). The aim is to recruit 59 PCPs from urban and rural areas in the regions of Frankfurt, Marburg-Biedenkopf as well as central and northern Hesse in the study. Each PCP will be asked to recruit six patients from their practice.

### Eligibility criteria {10}

The inclusion criteria for PCPs are:Willingness to recruit six eligible patientsWillingness to use the digital communication platform for rehabilitation care planningParticipation in the interview study is optional

There were no specified exclusion criteria for PCPs.

The inclusion criteria for patients are:Age 40 to 60 yearsIn total a minimum of 4-week (20 workdays) work disability due to musculoskeletal, oncologic or psychological conditions or the PCS within the last 6 months prior to study inclusion (patient-reported information)High risk of early retirement (determined with a scores ≤ 36 on the Work Ability Index [20])Participation in the interview study is optional

Exclusion criteria for patients are:Primary disease addiction or cranial brain traumaOngoing application for rehabilitation treatmentBeing retired, receiving a retirement pension or disability benefits or ongoing applicationBeing covered by private health insuranceWorking as a civil servantPermanently living abroadInability to speak and read sufficient German to read the study information and complete assessmentsHealth issues that prevent participation in rehabilitation therapy

### Who will take informed consent? {26a}

PCPs and eligible patients will be included in the study respectively at a personal appointment with the study team, at which the informed consent will be signed. The materials of the informed consent are presented in Additional file 2 in the original language. For more details on the recruitment procedure see SPIRIT item 15.

### Additional consent provisions for collection and use of participant data and biological specimens {26b}

Possible further follow-up assessments with patients are planned beyond the scope of the study. After taking part in the study, patients are therefore asked for their written consent to be contacted by the German Pension Insurance 5 and 10 years after participating in the study.

